**Care of Personal Information**

Participants will be allocated a unique code so that anonymity is protected**. All data and questionnaire responses will be anonymised.**

Data will be kept on password-protected computers that can only be accessed by the research team.

If permission is granted and the data is useful then anonymised data will be made available to other researchers via an ‘open’ repository at the end of the study.

Data security: Data will be stored for 10 years. Anonymised data (e.g. participant ID of the form A0001) will be held securely on an Ulster-based repository. Further information on this repository can be found at:

<http://uir-data.ulster.ac.uk/policy.html>

Governance of data for the focus groups part of the study:

Participants will be made aware that confidentiality will be maintained but the research team will be unable to prevent other members that participate in online focus groups and to adhere to this confidentiality agreement. Participants will also be informed that if they withdraw from this part of the study that once data has been anonymised it may be difficult to remove it.

Further information can be found at:

https://www.ulster.ac.uk/about/governance/compliance/gdpr

References.

*Gynaecological Cancer Research Charity.* (2020) Available at: <https://eveappeal.org.uk/> [Accessed Apr 22, 2021].

Al Maqbali, M. (2019) Exercise Interventions to Manage Fatigue in Women With Gynecologic Cancer: A Systematic Review. *Oncology Nursing Forum,* 46(1), 71-82.

Barbour, R.S. (2008) *Doing Focus Groups.* London: SAGE Publications. Available at: <http://ebookcentral.proquest.com/lib/ulster/detail.action?docID=783519>

**Statistical Model**

**Outcome measures**

Primary Outcome

The feasibility and acceptability of the study will be assessed in line with the MRC guidance on Developing and evaluating complex interventions (Craig 2019). These outcomes will assess participants that have completed or take part in the intervention part of the study and will be the following:

1. Adherence- interventions will run over 8 weeks. The completion of 4 weeks for mindfulness and 30min of home-based exercise weekly for two thirds (67%) of the duration of the trial will be regarded as adherence to the program. These levels of adherence are based on previous studies that have used the same levels (Mock *et al.* 2005; Pinto *et al.* 2005; Kim *et al.* 2019; Park *et al.* 2020) This will be assessed through the electronic diaries/logs that participants will be encouraged to complete along with the website/app data information- on frequency and duration of participant engagement with each session.
2. Attrition-We will estimate, following a review of web-based mindfulness intervention studies that the attrition rate will be approximately 20% with 10% to 15% of missing data (Carlson *et al.* 2019; Subnis *et al.* 2020).
3. Time to recruit, recruitment and retention rates, reasons for non-participation and acceptability of data collection. Time to recruit, recruitment and retention rates will be gathered through administrative data during (pre)screening, enrolment, allocation and follow-up. Reasons for non-participation, intervention/study dropouts will be collected when possible. Acceptability of data collection will be retrieved through missing data within questionnaires.
4. Acceptability of the programme will be assessed using focus groups this will include participants experience on the virtual delivery and data collection along with their experience and reflections on the exercise and mindfulness components of the intervention. A detailed description of these focus groups can be found in the protocol page 8,9 & 10.

Secondary Outcomes

Will include fatigue, QOL, sleep, anxiety and depression and mindfulness all of which will be assessed using self-report measures which are described in detail in the protocol page 6 & 7 and appendix 6.

**Sample size**

The sample size for this study is based upon feasibility and review of similar studies. The literature demonstrates that feasibility studies with similar interventions and methodologies within the cancer population recruit on average 40 participants in total (Eyles *et al.* 2015; Victorson *et al.* 2017; Price-Blackshear *et al.* 2020). Therefore it is anticipated that this study will recruit a total of 40 participants with 20 in each arm of the study.

**Statistical methods**

Descriptive statistics will be performed to produce mean values and standard deviations. Groups will be compared at baseline using independent t-test (two independent samples) for continuous data, and the chi-square test for independence for categorical data.

Primary analyses will be performed using the intention to treat on all data and using imputation method where outcomes are missing. Alpha will be set a priori at a level of P = .05. Repeated-measures ANOVAs will then be used to determine the effects of exercise and mindfulness and mindfulness intervention on changes in all outcomes of interest.

As this is a feasibility study and preliminary efficacy study, effect sizes (Cohen’s d) will be calculated by taking the mean difference and dividing by the pooled standard deviation to better estimate the meaningfulness of change for each observed outcome following the intervention. The values and meanings for effect size estimates are a small effect size (d = .2), a moderate effect size (d = .5), and a large effect size (d = .8).

Corelation analysis will be performed to determine whether changes in mindfulness/exercise are associated with changes in fatigue, anxiety, depression or sleep.

References.

Craig, P.e.a. (2019) Medical Research Council Developing and
evaluating complex
interventions.

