To explore the feasibility of conducting an 8- week online mindfulness and home-based walking and strength training programme for the management of cancer related fatigue in women with gynaecology cancer. The following objectives will assess feasibility outcomes:

1. To assess participant intervention adherence, study retention and attrition rate.
2. Explore the acceptability of using an online platform for the delivery and data collection of the exercise and mindfulness programme.
3. Explore the perspectives of participants concerning satisfaction (eg the intervention and its’ delivery) perceived value, barriers and facilitators of the online programme.

Secondary aim

To evaluate the effect of an 8 week exercise and mindfulness programme on cancer related fatigue as a primary clinical outcome and the effect on anxiety, depression, sleep and QoL as a secondary clinical outcome in an online setting.

Section 2 Methods

Study design

The study design and development have been reviewed and feedback considered from 2 patient and public involvement representatives.

This design will involve 2 parts firstly, an intervention part which is designed as an open, randomised, control trial with 1:1 allocation to either the mindfulness only group or the exercise and mindfulness group.

Following the intervention the second part will be online focus groups which will be conducted with participants once they have completed the intervention.

Study setting

Both parts of this study, intervention and focus groups, will be conducted online via a web-based, mobile application interface. Participants will be notified that data usage with this app will be minimal and battery usage of mobile devices may increase requiring additional charging of device. Therefore, participants should not incur any additional financial burden.

Participants & Eligibility

Eligibility criteria:

Inclusion criteria:

1. Women >18 years old and able to speak and read English.
2. Diagnosed with stage I-IV gynaecology cancer including endometrial, ovarian, cervical, vaginal, vulva, fallopian tube.
3. A minimum of 3 months post-treatment and up to 5 years.
4. Experiencing fatigue and at screening have a numerical rating score of $\geq$4 on a scale of 0-10.
5. Currently sedentary (exercising < once a week for 20 minutes at a vigorous intensity or, two times per week for 30 minutes at moderate intensity or < 20 minutes three times per week, for the past 6 months).

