The feasibility and acceptability of the study will be assessed in line with the MRC guidance on Developing and evaluating complex interventions (Craig 2019). These outcomes will assess participants that have completed or take part in the intervention part of the study and will be the following:

1. Adherence- interventions will run over 8 weeks. The completion of 4 weeks for mindfulness and 30min of home-based exercise weekly for two thirds (67%) of the duration of the trial will be regarded as adherence to the program. These levels of adherence are based on previous studies that have used the same levels (Mock *et al.* 2005; Pinto *et al.* 2005; Kim *et al.* 2019; Park *et al.* 2020) This will be assessed through the electronic diaries/logs that participants will be encouraged to complete along with the website/app data information- on frequency and duration of participant engagement with each session.
2. Attrition-We will estimate, following a review of web-based mindfulness intervention studies that the attrition rate will be approximately 20% with 10% to 15% of missing data (Carlson *et al.* 2019; Subnis *et al.* 2020).
3. Time to recruit, recruitment and retention rates, reasons for non-participation and acceptability of data collection. Time to recruit, recruitment and retention rates will be gathered through administrative data during (pre)screening, enrolment, allocation and follow-up. Reasons for non-participation, intervention/study dropouts will be collected when possible. Acceptability of data collection will be retrieved through missing data within questionnaires.
4. Acceptability of the programme will be assessed using focus groups this will include participants experience on the virtual delivery and data collection along with their experience and reflections on the exercise and mindfulness components of the intervention it will be achieved in the following way:

Design

Qualitative data collection utilising online focus groups will be facilitated via the Microsoft Teams (MS Teams) interface. This format for focus group has advantages including less dropout, more relaxed participants resulting in better communication, a more diverse group as able to include participants that are further away and cost-effective (Halliday *et al.* 2021)

Participants

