Will include fatigue, QOL, sleep, anxiety and depression and mindfulness all of which will be assessed using self-report measures as described earlier.

Participant timeline

Please see Appendix 14.

Timeline for Study

| Task | Months 2021-2023 | | | | | | | | | | | | | |
| --- | --- | --- | --- | --- | --- | --- | --- | --- | --- | --- | --- | --- | --- | --- |
|  | Sep-Dec | | | | Jan-Mar | | Apr- Jun | | Jul-Sep | Oct-Dec | | | Jan-Mar | Apr-Jun |
| Peer review |  |  | | |  | |  | |  |  | | |  |  |
| Filter committee |  |  | |  |  | |  | |  |  | | |  |  |
| UU REC |  | |  | |  | |  | |  |  | |  | |  |
| Mobile App Development |  | | | |  |  |  | |  |  | |  | |  |
| Intervention group recruitment |  | | | |  |  |  | |  |  | |  | |  |
| Focus groups |  | | | |  | |  |  |  |  | |  | |  |
| Data analysis |  | | | |  | |  | |  |  |  |  | |  |

Ethics and dissemination

Ethical approval will be sought from the Nursing/Health Science filter Committee and University of Ulster Research Ethics Committee (UREC).

The findings of the research will be communicated with those who participated in the study either via email or a local event. The researcher will disseminate the projects findings and outputs via oral and poster presentations at local, national and international conferences and publications in peer reviewed journal papers.

Confidentiality

Governance of Data for intervention part of study:

Data will be anonymised, and stored securely. Databases will be encrypted, as will any transferred data. The key to the participant IDs will be held by the Chief Investigator. Access to the anonymised data will use authentication and be traceable by login details.

If a person withdraws from the study their data will kept for 10 years, participants will consent to this (appendix 5). Personal data will only be retained for the duration of the study. Further information on data handling can be found at:

<https://www.ulster.ac.uk/__data/assets/pdf_file/0003/75639/DataHandling.pdf>

This is a self-management project. As such, access to the app will be via download. This app is a protype that will be developed in collaboration with the School of Computing at Ulster University. Pilot testing of this app will take place with the 2 Patient and Public Representatives and an additional 3 service users resulting in 5 testers altogether.

Data from the app will be uploaded securely to a secure server housed in the Data centre at Ulster University Coleraine Campus.

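### The analysis labelled primary (imputed repeated-measures ANOVA at unadjusted .05) can apply only to the secondary questionnaire scores, not to the primary feasibility outcomes

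*Protocol*

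**What the plan says.** Under Primary Outcome, repeated in the Statistical Model part, the protocol states: "The feasibility and acceptability of the study will be assessed in line with the MRC guidance". The items listed are adherence, attrition, recruitment and retention with acceptability of data collection, and acceptability of the programme from focus groups. Attrition is expected to be about 20%, with 10% to 15% missing data.

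The Secondary Outcomes "Will include fatigue, QOL, sleep, anxiety and depression and mindfulness". Under Secondary aim, the programme's effect is to be evaluated "on cancer related fatigue as a primary clinical outcome", with the other clinical measures ranked below it.

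Sample size gives 40 in total, 20 per arm, taken from the average size of similar feasibility studies. No effect size, standard deviation or precision target is used.

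Statistical methods describes the lead analysis in this way: "Primary analyses will be performed using the intention to treat on all data and using imputation method where outcomes are missing". The next sentence fixes the significance level at .05, with no adjustment for the number of tests. The section then names the test and its scope: "Repeated-measures ANOVAs will then be used to determine the effects of exercise and mindfulness and mindfulness intervention on changes in all outcomes of interest". Finally, Cohen's d is to be read against fixed benchmarks: "a small effect size (d = .2), a moderate effect size (d = .5), and a large effect size (d = .8").

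**The concern.** The word primary is attached to two different things. The primary outcome is a set of rates and qualitative findings. The primary analysis is a set of significance tests on questionnaire scores. Followed literally, the plan gives imputed ANOVA p-values the leading place and states no analysis for the feasibility rates. Imputation is also misplaced for the primary outcome, because attrition and missing questionnaire data are themselves feasibility results.

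If the ANOVAs are read as the main result, a sample chosen for feasibility is asked to answer an efficacy question. A real moderate effect would probably be missed, a chance finding among six scores would be fairly likely, and a verbal label on d would hide how little the data can say.

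**Working it through.** **Which outcomes the stated methods can analyse**

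| Outcome | Rank in protocol | Can a two-timepoint ANOVA with imputation apply? |
|---|---|---|
| Adherence, attrition, recruitment and retention, questionnaire completeness | Primary | No: proportions, rates and times, with no baseline-to-post score |
| Acceptability from focus groups | Primary | No: qualitative |
| Fatigue, QoL, sleep, anxiety, depression, mindfulness | Secondary | Yes |

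Every outcome that fits the stated primary analysis is secondary, and no primary outcome fits it.

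**Sample size.** The only arithmetic in the plan is 20 + 20 = 40. There is no power calculation to reproduce.

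**Power.** Inputs from the protocol: 20 per arm, 20% attrition, alpha .05, d = .5 (its moderate benchmark). Assumptions: two-sided test; complete data on the women remaining; d in baseline SD units.
- Women per arm after attrition: 20 × 0.8 = 16.
- With two timepoints, the group-by-time test in a repeated-measures ANOVA is a t-test on change scores. With equal SDs at both times and baseline-to-post correlation r, the effect in change-score SDs is d / √(2(1 − r)). Power comes from the noncentral t with 30 df and noncentrality (that effect) × √(16/2).

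| Assumed r | Effect in change-score SDs | Power at d = .5 | d needed for 80% power |
|---|---|---|---|
| .3 | .5 / 1.183 = .423 | 21% | 1.21 |
| .5 | .5 / 1.000 = .500 | 28% | 1.02 |
| .7 | .5 / .775 = .645 | 42% | 0.79 |

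The r = .5 row equals a plain two-sample t-test. With all 20 per arm retained, the three powers are 26%, 34% and 51%. The protocol gives no correlation, so the range is the honest answer.

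**False positives.** Six scores are listed, each tested at .05 with no adjustment stated.
- If independent: 1 − .95⁶ = 1 − .735 = 26%.
- Simulated two-sample t-tests, 16 per arm, with equal correlation among the six scores: about 24% at .3, 21% at .5, 16% at .7.

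The protocol's introduction describes depression, insomnia and fatigue as a symptom cluster, so some positive correlation is likely and 26% is an upper figure.

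**Precision of d.** For a between-arm d of .5 at 16 per arm:
- SE = √(2/16 + .5²/(4 × 16)) = √(.1250 + .0039) = .359.
- 95% CI: .5 ± 1.96 × .359 = −0.20 to 1.20.

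The interval includes no effect and runs past the large benchmark of .8.

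**What the primary analysis could deliver.** At the expected attrition, 8/40 = 20%, with exact 95% CI 9.1% to 35.6%. That is imprecise, but it bears directly on the primary aim.

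**The case against.** The best defence is that primary analyses loosely means main analyses, or names the intention-to-treat set, with the ANOVAs simply following. The protocol also calls the trial a preliminary efficacy study. The loose reading is possible, but it does not remove the problem: the main analysis would still consist of tests on secondary outcomes. Preliminary efficacy is served by estimates with intervals, which need no .05 threshold.

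Four stronger readings are tempting, and the documents do not support them.
- A reader might infer that fatigue is ranked inconsistently. It is called "cancer related fatigue as a primary clinical outcome" within the secondary aim and is listed first among the secondary outcomes. These are compatible. The ranking is merely not carried into Statistical methods.
- A reader might infer that missing confidence intervals for the feasibility rates are an error in themselves. That detail could sit in a separate SAP. The fault here is what the section does state as primary.
- A reader might infer that progression or an efficacy claim will turn on P < .05. No progression decision is stated, and no conclusion is tied to the threshold.
- A reader might infer that 40 is the wrong sample size, or that the tests are underpowered in every case. Forty is openly a feasibility number. At d = .8 and r = .7, power is 81% with 16 per arm, although no such scenario is offered as a design basis.

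It is also fair that the protocol does not say whether d is between or within arms. The interval above holds for a between-arm d only.

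**Conclusion.** The point holds: as written, the primary analysis does not analyse the primary outcome, whatever values are assumed in the calculations. Their role is to show why the ANOVAs should not lead. Power for a moderate effect is about 28%, and 21% to 42% over the assumed correlations. The chance of at least one false positive over six tests is at most 26%, and about 16% to 24% if the scores are correlated as assumed. A moderate d is compatible with anything from no effect to a large one. These figures rest on two-sided testing, 16 analysed per arm, and correlations the protocol does not supply. It should be corrected, but it is a fault of analysis wording and does not affect design, recruitment or data collection.

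**What to change.** Reword Statistical methods along these lines:
- The primary analysis estimates the feasibility outcomes with 95% CIs and without imputation. Adherence, attrition and retention, and questionnaire completeness use randomised women as the denominator. The recruitment rate uses those screened or approached. Focus-group acceptability stays with the thematic analysis already described.
- The 20% attrition and 10% to 15% missing-data figures are expectations for comparison, not criteria.
- Clinical outcomes are secondary and exploratory, with fatigue first as in the Secondary aim. Each is reported as a between-arm difference, and d, with its 95% CI.
- If the ANOVAs are kept, their p-values are labelled exploratory. No efficacy conclusion rests on P < .05 or on a small, moderate or large label.

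The cost is a few sentences. The downside is that the report will have no headline p-value for preliminary efficacy.

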If participants are interested in the study they can self-refer and a contact number for the researcher will be made available through the leaflets, social media or service providers. Participants can call the researcher for further information and if willing and interested screening for eligibility will be performed by the researcher (appendix 3). Once this is complete and it is established that participants meet the criteria participants will be e-mailed participant information sheet by the researcher (appendix 4) and time given to read and ask any questions regarding this. Participants can contact the research team if they have any further questions. Consent (Appendix 5) will be obtained after participants have been given one week to consider the study. An Qualtrics link to an electronic version of the consent will be emailed to participants.

Randomisation

Participants will be randomly allocated to either group through 1:1 allocation. Participants will be randomly assigned using computer-generated random number tables. A researcher/statistician not involved in treatment delivery or collection of outcomes will generate the random allocation sequence. Concealment of treatment allocation will be by placing individual random assignments into serially numbered sealed envelopes and be held by researcher/statistician not involved in treatment or outcome measure collection.

Participants will be notified of which group they have been allocated to via the e-mail they have supplied. A member of the research team will e-mail the participant with this information.

Data collection methods

Outcome measures

Data collection for outcome measures will be self-report measures using valid and reliable tools for measuring these outcomes. Participants will be asked to complete these assessments following randomisation at baseline and on completion of the programme. At baseline participants will also complete demographic information such as age, cancer type, education, income, and education (appendix 6). All of this will be done via Qualtrics (appendix 7), an e-mail reminder will be sent 2 weeks after the initial invitation if completion has not occurred. Access to intervention will only happen once all baseline assessments have been completed.

The following self-report measures will be used to assess outcomes at baseline and post-intervention (copies and links to Qualtrics of all can be found in appendix 7).

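### Clinical outcomes are to be analysed as changes by repeated-measures ANOVA without baseline adjustment; ANCOVA on data already collected would be more precise, by about 11–27% in variance if the baseline–outcome correlation is 0.4–0.7 (assumed)

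*Protocol*

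**What the plan says.** The Statistical methods section of the protocol fixes the analysis of the clinical outcomes: "Repeated-measures ANOVAs will then be used to determine the effects of exercise and mindfulness and mindfulness intervention on changes in all outcomes of interest". It adds "Alpha will be set a priori at a level of P = .05" and plans an intention-to-treat analysis "using imputation method where outcomes are missing". Baseline values enter in one other way only: "Groups will be compared at baseline using independent t-test (two independent samples) for continuous data", with chi-square tests for categorical variables. Nothing in the section adjusts the outcome comparison for baseline.

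The Data collection methods section and the Study Timeline in Appendix 14 show two assessments of every questionnaire, one at baseline and one after the intervention.

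On numbers, the Sample size section says "it is anticipated that this study will recruit a total of 40 participants with 20 in each arm of the study" and gives the reason: "The sample size for this study is based upon feasibility and review of similar studies". The attrition item under Primary Outcome expects that "the attrition rate will be approximately 20% with 10% to 15% of missing data".

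The primary aim is feasibility. Fatigue is the leading clinical outcome of the secondary aim, and the Statistical methods section also describes the study as one of preliminary efficacy.

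**The concern.** With one baseline and one follow-up value per woman, a two-arm repeated-measures ANOVA has a single term that answers the between-arm question, the group-by-time interaction. That interaction is a comparison of mean change scores. A change score uses the baseline value with its slope fixed at 1, whereas the data would normally support a smaller slope. This has two consequences.

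- The estimate is noisier than it need be, in a trial with at most 40 women.
- If the arms differ at baseline by chance, the change-score estimate moves in the opposite direction: the arm that starts worse tends to appear to improve more. The planned baseline tests do not correct this, because they examine differences that randomisation produces by chance and lead to no adjustment.

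At stake is the width and stability of the between-arm estimates for fatigue, quality of life, sleep, anxiety, depression and mindfulness, and of any effect sizes read from them.

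**Working it through.** **Inputs from the protocol.** 40 women, with "Participants will be randomly allocated to either group through 1:1 allocation", so 20 per arm; about 20% attrition with 10–15% missing data; alpha 0.05 (two-sided assumed); two assessments. There is no SD, no baseline–outcome correlation and no power calculation, so the plan has no precision figure to reproduce. The correlation r is an assumption throughout, and equal SDs at both times are assumed.

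**Women with observed outcomes.** 40 × 0.80 = 32 after attrition. If missing data compound on that, 32 × 0.90 = 28.8 and 32 × 0.85 = 27.2, giving 27–32. If the two rates are simply added, 40 × 0.70 = 28 and 40 × 0.65 = 26. The planned set with imputation is nominally 40.

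**Equivalence of the tests.** In a simulated data set of 32 women, the squared t statistic on change was 2.5018 and the group-by-time F was 2.5018.

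**Variance of the treatment effect, in units of SD² × 2/n (n per arm).**

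- Change score: 2(1 − r)
- ANCOVA: 1 − r²
- Ratio, ANCOVA to change: (1 + r)/2, so the large-sample share of precision lost is (1 − r)/2
- Estimating the slope multiplies the ANCOVA variance by about 1 + 1/(N − 4), with N the total: 1.043 at N = 27 and 1.036 at N = 32

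| r (assumed) | Change | ANCOVA | Loss, large sample | Net loss, N = 27 | Net loss, N = 32 |
|---|---|---|---|---|---|
| 0.3 | 1.40 | 0.91 | 35% | 32.2% | 32.7% |
| 0.4 | 1.20 | 0.84 | 30% | 27.0% | 27.5% |
| 0.5 | 1.00 | 0.75 | 25% | 21.7% | 22.3% |
| 0.6 | 0.80 | 0.64 | 20% | 16.5% | 17.1% |
| 0.7 | 0.60 | 0.51 | 15% | 11.3% | 12.0% |
| 0.8 | 0.40 | 0.36 | 10% | 6.1% | 6.8% |
| 0.9 | 0.20 | 0.19 | 5% | 0.9% | 1.6% |

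Simulation with 10,000 trials per setting agreed. For r = 0.4, 0.5 and 0.7 the net loss was 27.1%, 22.3% and 12.0% at N = 27, and 28.1%, 21.8% and 11.1% at N = 32. The choice of N matters little: at N = 40 the formula gives 28.1% at r = 0.4 and 12.6% at r = 0.7.

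**Interval width at 16 per arm, r = 0.5.**

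- Change: t(30 df) × √1.00 × √(2/16) = 2.042 × 0.354 = 0.72 SD
- ANCOVA: t(29 df) × √0.75 × √(2/16) × √1.036 = 2.045 × 0.866 × 0.354 × 1.018 = 0.64 SD

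**Chance baseline imbalance.** Given a baseline difference D, the expected difference at follow-up is the treatment effect plus rD. Subtracting D leaves the treatment effect minus (1 − r)D. At 20 per arm the standard error of D is √(2/20) = 0.32 SD. An imbalance of that size at r = 0.5 shifts the change-score estimate by 0.5 × 0.32 = 0.16 SD, against the 0.2 that the protocol calls a small effect.

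**The case against.** The planned method is a recognised one. Under randomisation, with baseline unaffected by allocation, it is unbiased over repeated trials and keeps its type I error. It contradicts nothing in the protocol, the sample size is not power-based, and the primary outcomes are adherence, attrition, recruitment and acceptability. All of that stands. It limits the point to an efficiency improvement for the secondary aim.

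A reader might infer several stronger things that the document does not support.

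- **A loss of 15–30% as a fact.** That range is the large-sample figure for r = 0.4–0.7. The protocol gives no r, and the cost of estimating the slope lowers the range at this size.
- **Baseline imbalance carried in full into the effect.** The shift is −(1 − r)D: only part of D, and opposite in sign.
- **The group main effect read as the treatment effect,** which would halve it. The text speaks of effects on changes, which points to the interaction.
- **An inflated type I error from imputation.** No imputation method is named. That detail may sit in an analysis plan, and multiple imputation fits the wording equally well.
- **Chi-square tests unsuitable in general.** Sparse cells can be argued for cancer type, with its six response options, but not for every categorical variable.

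One objection bears on the remedy. Baseline questionnaires are completed after randomisation in an open trial, and women are told their group by e-mail. The protocol does not say that the questionnaires come first. If they do not, baseline differences need not be pure chance. A model that forces equal baseline means then cannot be treated as interchangeable with ANCOVA. Change scores and ANCOVA also both use that baseline value, so neither is immune.

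**Conclusion.** The point holds as a matter of precision. The protocol commits to a change-score comparison where a baseline-adjusted one is available from the same data. If r lies between 0.4 and 0.7, about 11–27% of precision (variance scale) is lost at 27–32 women with observed outcomes. The loss is larger for a weaker correlation and close to nothing at r = 0.9. In interval terms this is 0.72 SD against 0.64 SD at 16 per arm and r = 0.5. The figures rest on the assumed r, on equal SDs at the two times, and on the protocol's own attrition and missing-data rates.

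The planned analysis is not invalid, and the feasibility conclusions do not depend on it. The change is worth making because the gain is nearly free.

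**What to change.** In Statistical methods, replace the repeated-measures ANOVA sentence with:

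> Each clinical outcome on completion of the 8-week programme is compared between arms by ANCOVA adjusted for its own baseline value, reported as adjusted mean difference with 95% CI.

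Remove the baseline t-tests and chi-square tests and tabulate baseline characteristics by arm descriptively.

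Do not use a model that assumes equal baseline means unless the baseline questionnaires are completed before women learn their allocation. The protocol should state that order.

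The cost is a few lines of wording. Baseline completion is already required before access to the intervention, so no extra data, contact or participants are needed.
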